## Methods

### Study Design

For this study, an open-label, nonrandomized controlled trial study design will be used to compare the efficacy and feasibility of the web-based program with the in-person treatment option in a controlled manner. Blinding will not be possible, as patients will be aware of whether their treatment is occurring in person or remotely. Qualitative focus groups will be conducted with patients to gather personal, social, and cultural factors. These focus groups will be conducted to allow for a natural and open conversation on how participant factors can impact the treatment experience with the program. Additional focus groups will be conducted with therapists to gather information regarding the feasibility of implementing a web-based psychotherapy tool. This will be done to better understand how web-based treatment compares with in-person in terms of usability, time efficiency, and perceived connectedness to patients. These focus groups will occur posttreatment.

Quantitative analyses of e-CBT treatment efficacy will be conducted using standardized and clinically validated symptomology questionnaires. This data collection will occur at baseline, at week 6 and week 12 (posttreatment), and at a 6-month follow-up. In addition, a qualitative analysis of focus group interviews will be conducted with theme extraction. We hypothesize that the e-CBT program will offer results comparable with those of the in-person treatment program regarding symptom reduction and quality of life improvement. On the basis of this design, both the efficacy and feasibility of the e-CBT program can be evaluated and compared with in-person treatment for MDD. All study procedures have been approved by the Queen’s University Health Sciences and Affiliated Teaching Hospitals Research Ethics Board (HSREB; file number 6020045).

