### Participants

Patients (N=110; 55 e-CBT participants and 55 in-person CBT participants) aged between 18 and 65 years will be recruited from Queen’s University from the outpatient psychiatry clinic at both the Kingston Health Sciences Center sites (Hotel Dieu Hospital and Kingston General Hospital) as well as from Providence Care Hospital located in Kingston, Ontario, Canada. Additionally, family doctors, physicians, clinicians, and self-referrals will be accepted. Once informed consent is provided, a psychiatrist from the research team will evaluate participants through a secure video appointment to make or confirm a diagnosis of MDD using the Diagnostic and Statistical Manual of Mental Disorders, 5th edition [31].

The inclusion criteria for the study are as follows: aged at least 18 years at the start of the study, diagnosed with MDD according to Diagnostic and Statistical Manual of Mental Disorders, 5th edition by an attending psychiatrist from the research team, competence to consent to participate, ability to speak and read English, and consistent and reliable access to the internet. Exclusion criteria are as follows: active psychosis, acute mania, severe alcohol or substance use disorder, and/or active suicidal or homicidal ideation. If a participant is receiving another form of psychotherapy, they will also be excluded from the study to avoid any confounding effect on the efficacy of this e-CBT program. Participants are eligible for the study if they are receiving pharmacotherapy. However, they must be receiving the same drug and dosage for the duration of the study. If eligible for the study, participants will choose between the e-CBT program (n=55) or the in-person CBT offered individually through this program at Hotel Dieu Hospital (n=55).

During the informed consent process, all participants will be explained that this program is not a crisis resource and that they will not always have access to their therapist. In the case of an emergency, participants will be directed to the proper resources (eg, emergency department or crisis lines), and this event will be reported to the principal investigator of the study. The reasoning behind having a nonrandomized design and allowing patients to choose their treatment is to mimic a real-world setting in which patients have autonomy in their treatment decisions. We recognize that this could be a limitation of this study. We plan to conduct a randomized controlled trial in the future.

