### Data Analysis

This is a confirmatory study with previously established objectives and analyses. Initially, all data are examined for missing, nonsensical, and outlying variables. Missing data are treated as missing and not imputed (ie, will be analyzed on a per-protocol basis). The participants in this study were intentionally oversampled to account for dropouts or withdrawals. On the basis of previous research, an anticipated dropout rate of up to 30% was factored in. Using the PHQ-9 as the primary outcome, a 30% change is considered clinically significant. Therefore, a sample size of 55 participants in each arm of the study would be sufficient for detecting significant results with *P*=.05 and a power of 0.95. Data collection occurs at baseline (preintervention), in the middle of the study (week 6), immediately after the intervention (week 12), and at a 6-month follow-up. Using Mann-Whitney *U* tests, demographic information can be compared between participants who complete the program and those who withdraw prematurely in the hope of identifying possible differences between the two. Moreover, an intention-to-treat analysis will be conducted to evaluate the clinical effects of treatment on participants who withdraw prematurely. Linear regression analysis (for continuous outcomes) and binomial regression analysis (for categorical outcomes) will be used to identify variables associated with the outcome measures (PHQ-9, Quick Inventory of Depressive Symptomatology Questionnaire, and Quality of Life and Enjoyment Questionnaire). This will occur over the 4 measurement time points while controlling for demographic variables, including age and gender. In addition, a comparative analysis between both groups’ questionnaire scores will be conducted at all data collection time points using group and paired two-tailed *t* tests.

Other quantitative measures for the e-CBT group will be gathered by extrapolating recorded information directly through the OPTT platform (eg, the number of log-ins per day and the amount of time spent logged in). Qualitative measurement analyses will be conducted to inquire about the role of personal, social, and cultural factors in enabling or constraining the use of e-CBT. The findings will identify factors related to the utility, feasibility, and accessibility of e-CBT from the perspectives of users and providers. Interpretive qualitative methods are ideal for gathering in-depth descriptions of user experience and meaning.

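### The stated 0.95 power with 55 per arm is power to detect a difference or change, so it cannot be read as power to show that e-CBT is comparable with in-person CBT

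*Protocol article*

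**What the plan says.** All places are in the protocol article.

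- **Hypothesis** (Study Design; the abstract's Objective says the same): "We hypothesize that the e-CBT program will offer results comparable with those of the in-person treatment program regarding symptom reduction and quality of life improvement".
- **Size** (Participants): "Patients (N=110; 55 e-CBT participants and 55 in-person CBT participants".
- **Basis for the size** (Data Analysis): "Using the PHQ-9 as the primary outcome, a 30% change is considered clinically significant". The next sentence draws the inference that "a sample size of 55 participants in each arm of the study would be sufficient for detecting significant results". The significance level is set there at P=.05, alongside "a power of 0.95".
- **Dropout** (Data Analysis): "an anticipated dropout rate of up to 30% was factored in". Missing values are not imputed, and the analysis is described as per protocol; an intention-to-treat analysis is also mentioned.
- **Comparison of arms, by t tests** (Data Analysis): "a comparative analysis between both groups’ questionnaire scores will be conducted at all data collection time points using group and paired two-tailed".

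The same section calls the study confirmatory. It does not say whether the 30% is a change within an arm or a difference between arms. The article names no comparability margin and no confidence-interval rule.

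**The concern.** The hypothesis and the power statement concern different questions. The hypothesis is that two treatments give similar results. The sizing and the planned t tests are built to find that something differs or has changed. The 30% can be read in two ways, and neither makes 0.95 the power for the hypothesis:

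- **Within-arm change.** The 0.95 then describes whether patients improve from baseline and says nothing about e-CBT against in-person CBT.
- **Between-arm difference.** The 0.95 is then the chance of a significant result when one arm really is worse by a full clinically significant amount. That is the situation the hypothesis says does not hold.

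This is the only power figure in a study that calls itself confirmatory and whose stated hypothesis is comparability, so readers are likely to attach it to that hypothesis. A non-significant t test could then be taken as strong evidence of comparability, and the article's Conclusions and Discussion look ahead to wider care without loss of quality. The test alone would not support that.

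**Working it through.** **Inputs from the article.** 55 per arm; P=.05, taken as two-sided because the planned t tests are two-tailed; power 0.95; dropout up to 30%; a 30% PHQ-9 change.

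**Assumed inputs, not in the article.** Baseline PHQ-9 mean 15, so 30% is 0.30 × 15 = 4.5 points; SD 5.5, range 5 to 6; true between-arm difference zero for the comparability calculations; one-sided 0.025 for non-inferiority, which corresponds to a two-sided 95% interval. The half-size margin below is illustrative.

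**1. The plan's own figure.** It cannot be reproduced, because the article gives no SD or baseline mean. The implied effect can be solved for. With equal arms,

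d = (z₀.₉₇₅ + z₀.₉₅) × √(2/n) = (1.960 + 1.645) × √(2/n)

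- 55 per arm: 3.605 × √(2/55) = 0.687; exact t calculation 0.69.
- After 30% dropout, 55 × 0.7 = 38.5, about 38 per arm: 3.605 × √(2/38) = 0.827; exact t calculation 0.84.

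These d values need no assumed SD. In reverse, 38/(1 − 0.3) = 54.3, which rounds up to 55. So 55 is consistent with a between-arm difference of about 0.83 SD after dropout.

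**2. The two readings of the 30%.**

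- *Between arms:* d = 4.5/5.5 = 0.818. Power at 38 per arm is 0.94 (0.97 at SD 5, 0.90 at SD 6).
- *Within one arm*, with 5.5 taken as the SD of the change: about 22 patients give 0.95.

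Under these assumptions 55 per arm is enough, or nearly enough, to detect a 30% change on either reading. Neither calculation addresses comparability.

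**3. Power for comparability.** For non-inferiority with margin M and true difference zero,

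power ≈ Φ( M / (SD × √(2/n)) − 1.960 )

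Example, M = 2.25, SD 5.5, n = 38: 5.5 × √(2/38) = 1.262; 2.25/1.262 = 1.783; Φ(1.783 − 1.960) = Φ(−0.177) = 0.43. The exact t calculation gives 0.42. Exact results:

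| Margin | n per arm | SD 5 | SD 5.5 | SD 6 |
|---|---|---|---|---|
| 4.5 points (full 30%) | 38 | 0.97 | 0.94 | 0.90 |
| 4.5 points (full 30%) | 55 | 1.00 | 0.99 | 0.97 |
| 2.25 points (half) | 38 | 0.49 | 0.42 | 0.36 |
| 2.25 points (half) | 55 | 0.65 | 0.57 | 0.50 |

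By the formula in step 1, 0.95 power for non-inferiority needs a margin of at least 0.69 SD with 55 per arm, or about 0.83 SD with 38.

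**4. Expected precision.** The 95% interval half-width is t × SD × √(2/n). At SD 5.5:

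- 55 per arm: 1.982 × 5.5 × √(2/55) = 2.1 points.
- 38 per arm: 1.993 × 5.5 × √(2/38) = 2.5 points.

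**The case against.** The strongest defence is that nothing in the power statement is shown to be false. The Data Analysis section says only that 55 per arm is enough to detect significant results, and it never ties the 0.95 to comparability. The Objectives section also gives improvement of symptoms in patients with MDD as an aim, and paired t tests are planned, so a within-arm reading serves a stated purpose. On the between-arm reading, plausible values give about 0.94 even after the full 30% dropout. The missing SD may stand in a fuller protocol. All of this stands.

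A reader might go further and infer that the trial lacks the power it claims for its hypothesis. The article does not support that. Power for comparability is undefined until a margin and an SD are fixed. The low values in the table come from a half-size margin that appears nowhere in the article, and the full 30% used as the margin gives 0.94 at 38 per arm and 0.99 at 55 (SD 5.5). Nor does it follow that the trial cannot exclude a loss of half the 30% change. At 55 per arm and SD 5.5 the expected half-width of 2.1 points is below 2.25, and 38 per arm is the worst case of a dropout stated as an upper limit.

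The defence does not remove the mismatch. Even if the full 30% were the margin, the article would have to say so, accepting as comparable a loss of up to the size it calls clinically significant. It would also need an interval or non-inferiority rule in place of a two-tailed test of difference.

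**Conclusion.** The point holds as a mismatch between the hypothesis and the power statement with its tests. It is not an arithmetic error. The 0.95 is power to detect a difference or change based on a 30% PHQ-9 change whose meaning is not defined. It cannot be carried over to the comparability hypothesis, and a non-significant t test would not establish comparability.

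This conclusion needs no assumed figure; its size does. With a baseline of 15, SD 5 to 6 and no true difference, comparability power runs from 0.36 (half-size margin, 38 per arm, SD 6) to above 0.99 (full 30% margin, 55 per arm, SD 5). The declared margin largely decides where in that range the trial lies.

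**What to change.** No extra enrolment is needed. In the Data Analysis section:

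1. Say whether the 30% PHQ-9 change is within an arm or between arms.
2. Restate the power: 55 recruited per arm gives 0.95 power for a between-arm difference of d about 0.69 with no dropout, and about 0.84 with 38 evaluable per arm at 30% dropout.
3. Declare a comparability margin on the PHQ-9 with its justification, and judge comparability by whether the 95% confidence interval for the between-arm difference stays within it. Do not rely on a non-significant t test.
4. Give the power for that margin with the SD, sidedness and analysis set used, and the expected interval half-width (about 2.1 points at 55 and 2.5 at 38 per arm if the SD is 5.5).

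The article reports 52 and 48 participants already recruited, so the margin should be fixed without reference to outcome data and its date recorded. The cost is rewriting one paragraph, and a less favourable stated power if the margin is smaller than the 30% change.

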### Outcome Evaluation

The primary outcomes that will be measured include changes in symptoms of depression based on the following clinically validated symptomology questionnaires: Patient Health Questionnaire-9 (PHQ-9) and the Quick Inventory of Depressive Symptomatology Questionnaire [33,34]. An additional measurement of quality of life change will be made based on the Quality of Life and Enjoyment Questionnaire [35]. All questionnaires were shown to be reliable and highly valid. Questionnaires will be collected directly through OPTT before treatment (baseline), after session 6, after the final session (week 12), and after a 6-month follow-up. Participants will not be offered incentives to increase the completion of the questionnaires. OPTT will collect use statistics (ie, log-ins per day and amount of time spent logged in) to help better understand the relationship between engagement and treatment outcomes.

Through the focus groups, health care providers will be asked about the feasibility of providing the electronic-delivered psychotherapy program and how it compares with in-person psychotherapy delivery. They will be asked to make their judgments based on variables such as time commitment, connectedness to patients, and benefits and drawbacks. From the focus group interviews with the participants, personal, social, and cultural factors (eg, gender, sexuality, background, supportive resources, and structural or social barriers) will be extracted using an interpretive phenomenological analysis approach. In addition, any adverse events and adherence to the intervention will be reported.

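### The primary outcome is change in symptoms, but the arms are compared on scores with no adjustment for baseline, so with patient-chosen arms starting severity is mixed with response

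*Protocol article*

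**What the plan says.** All references are to the Protocol article.

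- **Outcome Evaluation** defines the endpoint as change: "The primary outcomes that will be measured include changes in symptoms of depression", measured by the PHQ-9 and the Quick Inventory of Depressive Symptomatology. Quality of life is treated the same way: "An additional measurement of quality of life change will be made".
- **Study Design** states the hypothesis as comparable results for symptom reduction and quality of life improvement, which are also changes.
- **Data Analysis** sets the visits: "Data collection occurs at baseline (preintervention), in the middle of the study (week 6), immediately after the intervention (week 12), and at a 6-month follow-up".
- **Data Analysis** gives the between-arm comparison: "questionnaire scores will be conducted at all data collection time points using group and paired two-tailed *t* tests".
- **Data Analysis** also plans linear and binomial regression, which "will be used to identify variables associated with the outcome measures", with the three questionnaires listed by name. It adds: "This will occur over the 4 measurement time points while controlling for demographic variables, including age and gender".
- **Participants** says that eligible patients choose between e-CBT and in-person CBT.

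**The concern.** The endpoint as defined and the comparison as planned are different quantities. A between-arm test on scores at week 12 asks which group is less depressed at week 12. The hypothesis asks which group improved more. The two agree on average only if the groups start level. Here nothing in the design makes them start level, because patients pick their own arm.

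Baseline appears in the analysis as one of the occasions on which the outcome is analysed. It does not appear as something to adjust for. If, say, more severely ill patients prefer one form of delivery, their higher starting score will still be partly visible at follow-up and will be read as a poorer response to that form. The trial's main conclusion, whether e-CBT is comparable with in-person CBT in reducing symptoms, rests on this comparison.

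**Working it through.** **The plan's own figure.** The only planning figure is 55 per arm, for P=.05, power 0.95, a 30% PHQ-9 change and up to 30% dropout. No PHQ-9 mean, SD or responder rate is given, so it cannot be reproduced. It can only be solved backwards, for scale. Two-sided, d = (1.960 + 1.645) × √(2/n), which is 0.687 SD at n = 55 and 0.822 SD at n = 55 × 0.7 = 38.5.

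**Step 1: what each planned analysis estimates.**

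| Planned analysis | Estimates | Difference in change between arms? |
|---|---|---|
| Group t test at each visit | difference in score at that visit | no |
| Paired t test | change within persons | no; separate results in the two arms are not a contrast between them |
| Regression over 4 visits, demographic covariates | correlates of the questionnaire measures; form not stated | not stated |

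Change from baseline does not exist at baseline. A regression over all four visits is therefore an analysis of change only if it is read through a time interaction, and none is named.

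**Step 2: effect of a baseline difference.** Work in SD units, e-CBT minus in-person. Let b be the baseline difference, assumed to persist, and δ the true difference in change.

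- Week-12 score contrast = b + δ
- Change contrast = (b + δ) − b = δ
- Contrast with the baseline score as covariate = (b + δ) − ρb, where ρ is the correlation between visits

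Assumed, since the document gives no values: δ = 0.50, b from −0.4 to +0.4, ρ = 0.5.

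| b | Score contrast | Change contrast | Baseline as covariate |
|---|---|---|---|
| −0.4 | 0.10 | 0.50 | 0.30 |
| −0.2 | 0.30 | 0.50 | 0.40 |
| 0 | 0.50 | 0.50 | 0.50 |
| +0.2 | 0.70 | 0.50 | 0.60 |
| +0.4 | 0.90 | 0.50 | 0.70 |

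The score contrast moves one for one with b. Its sign reverses once b falls below −δ: at b = −0.6 it is −0.6 + 0.5 = −0.10.

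**Step 3: predictors.** A variable that shifts the score by k at every visit has association k with the score at each visit, and k − k = 0 with change. If scores are the dependent variable, it is reported as associated with outcome although it says nothing about improvement.

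**Step 4: the pooled case, which the text does not state.** If one arm effect were fitted to all four visits with full data and no arm-by-time term, its expected value would be [b + 3(b + δ)]/4 = b + 0.75δ. With b = 0 and δ = 0.50 that is 0.375, an attenuation of 25%. With b = −0.4 it is −0.4 + 0.375 = −0.025, and with b = +0.4 it is 0.775. For t tests done visit by visit, the attenuation is zero.

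**The case against.** The strongest reply has three parts.

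1. **Change is not absent.** Paired t tests are planned and need the baseline visit. This stands as far as it goes, but they test change within persons and do not compare it between arms.
2. **The regression is a search for predictors, and its form is not given.** The text names no arm term, does not say that raw scores are the dependent variable, and does not say that visits share one effect. A model with time interactions would fit the same words, and a condensed article may leave that to the full protocol or analysis plan. This stands for the regression. It does not cover the group t tests, where scores are named explicitly, the visits are given and the method is fixed.
3. **Comparing arms at baseline is informative when patients choose.** This also stands: the comparison describes imbalance. It does not adjust for it.

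A reader might go further and infer that pre-treatment data dilute the arm difference by a quarter, pushing the result towards comparability. The document does not support that. The t tests are placed at each visit, so baseline data cannot enter the later contrasts. The 0.75 factor needs a pooled single arm effect that is nowhere stated. The direction also fails once baseline imbalance is allowed, since Step 2 shows error either way.

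**Conclusion.** The point holds as a mismatch between endpoint and analysis. The outcome and hypothesis concern change, but the only between-arm comparison spelled out is of scores, and no baseline score is named for adjustment. Under patient choice, any persisting baseline difference enters the follow-up contrast in full and can hide, exaggerate or reverse a difference in response.

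In the illustration a true difference of 0.50 SD appears as anything from 0.10 to 0.90 SD. That range rests on assumed values of δ and b and on the imbalance persisting in full. The one-for-one shift is algebra under that last condition. The document gives no baseline data, so the actual size and direction are unknown. A 25% attenuation would arise in addition only under a pooled regression with a single arm effect, and should not be claimed of this plan.

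**What to change.** In Data Analysis:

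- Make the between-arm comparison the difference in change from baseline in the PHQ-9, and likewise in the other two questionnaires, at week 6, week 12 and the 6-month follow-up.
- Estimate it by a model with the baseline score as covariate or, if all four visits stay in one model, by the arm-by-time contrast. State in advance which. When baselines differ the two need not agree (Step 2), because the covariate model removes only the share ρ of the imbalance. Neither removes other confounding from patient choice.
- Read predictor effects the same way, as associations with change.
- Keep the baseline comparison only as a description of group imbalance.

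**Cost.** Wording and a slightly more complex model; no new data or patients. Change scores are noisier than levels when the correlation between visits is low. With equal baselines, d = 0.822 and 38.5 per arm, a week-12 score t test has power 0.95. The change score has 0.861, 0.950 and 0.996 at ρ = 0.3, 0.5 and 0.7, and the baseline-covariate model has 0.966, 0.986 and 0.999. These correlations are assumed.

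### The planned regressions over four repeated visits do not say whether visits are pooled; pooled ordinary regression would understate standard errors for person-level variables, and separate fits would waste data.

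*Protocol article*

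**What the plan says.** All of the relevant text is in the Data Analysis section of the protocol article.

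- The method and its purpose: "Linear regression analysis (for continuous outcomes) and binomial regression analysis (for categorical outcomes) will be used to identify variables associated with the outcome measures". The outcomes are the PHQ-9, the Quick Inventory of Depressive Symptomatology and the quality of life questionnaire.
- How time enters: "This will occur over the 4 measurement time points while controlling for demographic variables".
- The visits: "Data collection occurs at baseline (preintervention), in the middle of the study (week 6), immediately after the intervention (week 12), and at a 6-month follow-up".
- A separate comparison of the two groups is made "at all data collection time points using group and paired two-tailed" t tests.
- Missing values are not imputed, and dropout of up to 30% is anticipated.

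The Results part of the abstract names the same two regressions as the analyses still under way. The article nowhere mentions a mixed model, generalised estimating equations (GEE), a random effect or a clustered standard error. Age and gender are the only regressors named; arm is not. Under Participants, patients choose their own arm.

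**The concern.** Each participant gives up to four scores per questionnaire, and scores from one person are correlated. A named linear or binomial regression, in its ordinary form, treats every row as independent. If the four visits are stacked in one such model, a variable that is fixed for a person is credited with more information than it has. Its standard error is then too small, and it is declared associated with outcome too often. Finding associated variables is the stated job of these regressions.

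Stacking also makes the baseline score an outcome alongside the scores it should help to explain. It precedes treatment, so a single pooled arm term, if one were fitted, would be diluted.

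If one model per visit is meant, the standard errors are sound, but the plan gives up information and multiplies tests. These regressions are the only analysis in the article that adjusts for any covariate, in a study where patients select their treatment, so it should be clear what is fitted.

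**Working it through.** **The plan's own figure.** The article gives no standard error or error rate for the regressions, so there is none to reproduce. Its one design figure is 55 per arm for power 0.95. That cannot be reproduced, because no PHQ-9 baseline mean or standard deviation is stated. Nothing below depends on it.

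**Inputs.**
- Scores per person, m = 4 (Data Analysis). With dropout some people have fewer, so m = 3 is also shown.
- Within-person correlation ρ: not in the article. Assumed equal between all pairs of visits, at 0.3, 0.5 and 0.7.
- Sample: 110 people, 55 per arm (Participants).
- Nominal two-sided level: 0.05.

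**Reading 1: visits pooled, ordinary regression, person-level variable.**

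Design effect D = 1 + (m − 1)ρ. The standard error is understated by a factor of √D. True error = 2[1 − Φ(1.96/√D)].

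| m | ρ | D | √D | True error |
|---|---|---|---|---|
| 4 | 0.3 | 1.9 | 1.38 | 0.155 |
| 4 | 0.5 | 2.5 | 1.58 | 0.215 |
| 4 | 0.7 | 3.1 | 1.76 | 0.266 |
| 3 | 0.3 | 1.6 | 1.26 | 0.121 |
| 3 | 0.5 | 2.0 | 1.41 | 0.166 |
| 3 | 0.7 | 2.4 | 1.55 | 0.206 |

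*Check by simulation.* 2,000 runs per correlation, 110 people, four complete visits, a normal outcome, and a model with group, age, sex and visit. Rejection rate for a group term with no true effect:

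| ρ | Pooled ordinary | Pooled, clustered on person | One visit only |
|---|---|---|---|
| 0.3 | 0.173 | 0.055 | 0.055 |
| 0.5 | 0.204 | 0.056 | 0.047 |
| 0.7 | 0.269 | 0.051 | 0.050 |

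The pooled column agrees with the formula to within two percentage points.

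*Within-person terms.* For time and arm-by-time the error runs the other way. The ordinary standard error is too large by 1/√(1 − ρ), which is 1.20, 1.41 and 1.83 at ρ = 0.3, 0.5 and 0.7.

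*Baseline as an outcome.* Suppose an arm effect δ is the same at all three later visits and zero at baseline, with visits equally weighted. A single pooled arm term then estimates (0 + δ + δ + δ)/4 = 0.75δ.

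**Reading 2: one model per visit.**

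Each model has one row per person, so independence holds and the error stays near 5% (last column of the simulation). The costs are different:
- Three questionnaires at four visits make 3 × 4 = 12 regressions. A variable with no true association gets 12 tests and an expected 12 × 0.05 = 0.6 false positives.
- At 30% dropout, a late visit has about 55 × 0.7 = 38.5 people per arm. Earlier scores from the rest add nothing to that visit's fit.

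**The case against.** The strongest objection is that the article never says the rows are treated as independent. Linear regression is a broad label, and one model per visit is an open reading that fits outcomes defined as changes in symptoms. A condensed article may also leave the covariance structure to a full protocol or analysis plan that is not shown. This stands in part: the understated standard errors are conditional on pooling. The wording leans towards pooling, since the regressions run over the time points while the t tests are made at each of them, but that does not settle it. The objection does not remove the point, because the article names a specific method for repeated data and neither reading of it is a good choice.

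A reader might infer that the comparison of e-CBT with in-person CBT is itself invalid. The documents do not support that. The direct comparison is by t tests: a group t test at one visit uses one score per person, and a paired t test allows for the pairing. Arm is not listed as a regressor, so the inflation reaches it only if it is entered.

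It is also fair to say that the 16% to 27% range rests on an assumed correlation and four complete scores per person. With three scores each the range is about 12% to 21%.

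**Conclusion.** The point holds in conditional form. The article commits to linear and binomial regression over four repeated visits without saying whether they are pooled.

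- If pooled with ordinary regression, person-level standard errors are understated by a factor of about 1.38 to 1.76, and a nominal 5% test has a true error of about 16% to 27%. Within-person terms err in the conservative direction. This rests on equal correlation of 0.3 to 0.7 and four scores each; both are assumptions.
- If fitted separately by visit, test size is correct, at the price of lost data and more tests.

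A repeated-measures model improves on the plan under either reading. This should be changed, but it bears on the adjusted, exploratory part of the inference and does not undermine the trial or its t tests.

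**What to change.** State in Data Analysis how the four visits enter the regressions, and replace those regressions with one repeated-measures model per questionnaire:

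- **Continuous scores:** a linear mixed model with week 6, week 12 and 6-month scores as outcomes; baseline score, time, arm, arm-by-time, age and gender as fixed effects; and a covariance structure for scores from the same person, unstructured if it can be fitted.
- **Any binary outcome:** GEE or a mixed logistic model, clustered on participant, with the same terms.
- **Baseline:** use it as a covariate and do not pool it with the post-treatment outcomes. Because participants choose their arm, say plainly that baseline adjustment does not remove confounding. Report as a sensitivity analysis a model that keeps baseline as a repeated outcome with an arm-by-time term. In a non-randomised comparison the two can give different answers, and the reader should see both.

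The t tests can stay as they are on this point. The cost is a few sentences and a little more analysis work in standard software; no new data are needed.
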